### Secondary outcome measures

The following secondary maternal outcomes measures will be collected; use of second instrument to achieve OVB, caesarean section, episiotomy, perineal trauma (1st, 2nd, 3rd, 4th degree tear), cervical tear requiring suturing, general anaesthesia and estimated blood loss (EBL). The following secondary neonatal outcomes will be collected; Apgar score at 1, 5, 10 min, Umbilical artery pH, shoulder dystocia, admission to Neonatal Intensive Care Unit (NICU), death within 28 days of birth.

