### Clinical variable characteristics

The following clinical variable characteristics will be collected and used for adjusting and comparing secondary clinical outcomes; maternal age (years), body mass index (BMI) at booking, parity, history of previous caesarean or vaginal birth, length of gestation (completed weeks), duration of first and second stage (minutes), indication for assisted vaginal birth (presumed fetal compromise, delay in 2nd stage, maternal exhaustion, other), rotation required as part of OVB (Yes/No), analgesia (epidural block, spinal block, general anaesthesia, pudendal block, perineal infiltration, none), baby birth weight (g), grade of operator (Speciality Trainee (years of residency in O&G) (ST) 1–2, ST 3–5, ST 6–7, Consultant), grade of supervisor (if applicable, ST 3–5, ST 6–7, Consultant).

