#### Main analysis

The outcome for the main analysis is the rate of successful attempted OVB in term infants, dichotomised into successful or failed. This dichotomous outcome measured for each birth will be analysed with a modified Poisson regression (with robust estimation of the variance) [16]. All models will be adjusted for hospital units as fixed to account for clustering at maternity unit level, i.e. correlation between births occurring in the same maternity unit. A formal mixed or marginal regression model cannot be considered due to the reduced number of hospital units involved in this study (n = four).

In the main analysis, we will assess the intervention effect (control periods vs. post-intervention periods) and include an adjustment for the time period (period zero to five) to account for any underlying time trend susceptible to confound the assessment of the main effect [17, 18]. We will either model the time periods with categorical fixed effect variables (with dummy indicators for each period) or as a continuous factor with appropriate polynomial function of time if required. Statistics such as the Aikeke information criterion will be used to select the best modelling for time.

The interaction between time and the main intervention effect will then be modelled to investigate the timing and duration of the intervention effect. The study is not powered for such interaction and this last model should be considered as exploratory.

We will use the Log-likelihood ratio or Wald test and *p*-value of 0.05 to assess the strength of the association, assuming that any p-value equal or below 0.05 (two-sided) will show evidence of an association between the intervention and outcome.

No interim analysis is planned.

The model will then be adjusted for patient, delivery or hospital characteristics susceptible to influence the primary or secondary outcome such maternal BMI, length of second stage of labour and fetal weight. These analyses will be conducted on an intention-to-treat principle, i.e. a unit will be considered as exposed to the intervention 3 months after the initial planed date of intervention implementation.

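### The covariate-adjusted models that follow the main model adjust for total second-stage length and for analgesia including general anaesthesia, both of which can be consequences of a failed attempt

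*Protocol article*

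**What the plan says.** The article's Main analysis section builds the analysis in stages. The first model has no clinical covariates: "In the main analysis, we will assess the intervention effect (control periods vs. post-intervention periods) and include an adjustment for the time period". Unit enters throughout: "All models will be adjusted for hospital units as fixed to account for clustering at maternity unit level". Near the end of the section comes a further step: "The model will then be adjusted for patient, delivery or hospital characteristics susceptible to influence the primary or secondary outcome". With its examples, the defining clause reads "susceptible to influence the primary or secondary outcome such maternal BMI, length of second stage of labour and fetal weight".

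The Clinical variable characteristics section gives a longer list of variables that "will be collected and used for adjusting and comparing secondary clinical outcomes". It includes the duration of the first and second stages in minutes, whether rotation was required, the grades of operator and supervisor, and "analgesia (epidural block, spinal block, general anaesthesia, pudendal block, perineal infiltration, none".

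The Secondary outcome measures section names among the maternal outcomes "cervical tear requiring suturing, general anaesthesia and estimated blood loss (EBL". Additional analyses applies the same modelling strategy to every secondary outcome.

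**The concern.** An adjustment variable should be settled before the event being modelled. Two of the listed variables are not.

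- **Length of second stage.** The stage ends at birth. The Primary outcome measure section says that failure with the first instrument leads to a second instrument or a caesarean. Both take time before the baby is born, so total length is partly produced by the primary outcome. The same holds when the outcome is second-instrument use or caesarean section.
- **Analgesia.** General or spinal anaesthesia may be given because the attempt failed, so it can lie downstream of failure. General anaesthesia is also an outcome in its own right, so the list as written allows it to be adjusted for itself.

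The adjusted model matters because implementation dates are not randomised, and a reader will look to that model for control of case mix. If its estimate moves toward no effect, the movement could be read as confounding removed when it is an artefact of the covariate. The Discussion says that equivocal or negative results should prompt redesign of the training, so the direction of the distortion has consequences.

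**Working it through.** The plan gives no figure for this point, so there is none to reproduce. The only input from the article is the design effect in the Sample size scenarios, failure falling from 20% to 10%, which is a risk ratio (RR) of 0.10/0.20 = 0.50. The article gives neither the spread of second-stage length nor the minutes that a failed attempt adds. Those values below are assumptions.

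**1. Linear approximation for second-stage length.** Let failure add d minutes, let length otherwise have standard deviation s, and let v be the variance of the failure indicator. With mean failure (20% + 10%)/2 = 15%, v = 0.15 × 0.85 = 0.1275. Adjusting for total length shrinks the effect by d²v/(s² + d²v).

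| d (min) | s (min) | d²v | Shrinkage |
|---|---|---|---|
| 30 | 60 | 114.75 | 114.75/3714.75 = 3% |
| 60 | 60 | 459 | 459/4059 = 11% |
| 60 | 45 | 459 | 459/2484 = 18.5%, about 19% |

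**2. Simulation with the planned modified Poisson model** (600,000 births, point estimates only). Assumptions: an unmeasured difficulty score raises log failure risk by 0.4 per SD; length is 90 min plus 20 min per SD of difficulty plus noise with SD 30 min; failure then adds 0 to 30 min. The unadjusted RR is 0.50.

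| Failure adds | Training does not change length | Training shortens it by 5 min | Training shortens it by 10 min |
|---|---|---|---|
| 10 min | 0.51 | 0.54 | 0.57 |
| 20 min | 0.52 | 0.57 | 0.62 |
| 30 min | 0.55 | 0.61 | 0.68 |

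The entries are RRs adjusted for total length. Leaving length out, or using length before the attempt, gives about 0.50.

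**3. Same set-up with no true effect on failure.** If training does not change length, the adjusted RR stays at about 1.00. If training shortens the stage by 5 to 10 min, the adjusted RR is about 1.03 to 1.21 (failure adding 0 to 30 min), a false suggestion of harm.

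**4. General anaesthesia as a covariate for the primary outcome**, assuming it is used in 1% of births after success and in 5%, 10% or 20% after failure. A true RR of 0.50 becomes about 0.50, 0.51 and 0.54.

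**5. General anaesthesia as outcome and covariate together.** If both record the same event, the outcome is always yes in the general anaesthesia category and always no in every other. No variation is left within categories for training to explain, so the adjusted RR is 1 or cannot be estimated, whatever the training did.

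**6. Operator grade, for contrast.** Assume that senior operators halve the failure risk and that training has a direct RR of 0.60. If training raises the senior share by 10 or 20 points, the total RR is 0.56 or 0.53 and the grade-adjusted RR is about 0.60. If the share does not change, adjustment changes nothing. Grade therefore matters only as a possible mediator, not as a consequence of failure.

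**The case against.** The strongest reply is that the headline estimate is untouched. The first model contains only intervention, unit and period, and the clinical covariates come in afterwards. That is correct. A reader might infer that the study's main training effect is biased, and the article does not support this.

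A second reply concerns scope. Of the disputed variables, only second-stage length is named in Main analysis. Analgesia, rotation and grade come from a list tied to secondary outcomes, and they reach the primary outcome only through the open wording of the adjustment sentence. No sentence says that analgesia will enter the model for general anaesthesia, and the covariate set for each outcome is commonly settled in the statistical analysis plan. This limits the general anaesthesia point to what follows if the list is applied as written. It does not rescue second-stage length, which is a stated choice and not a missing detail.

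A third reply is that rotation and operator or supervisor grade should not be swept in. A reader might infer that they too follow from failure. They do not: the need for rotation usually describes the case, and grade is normally set when the attempt begins. The comparison is non-randomised and before-after, and the article mentions trainees rotating between hospitals, so seniority may differ between periods for reasons unrelated to training. Adjusting for it may be legitimate. Because the course teaches rotational technique, these variables might also be mediators, but that is a question about the estimand and not an error.

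Finally, the size rests on assumed inputs. The 19% needs the most extreme pair tried, and RRs up to 0.68 need training to shorten the second stage, which the article does not claim. This stands and is reflected in the verdict.

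**Conclusion.** The point holds for two variables and only for the covariate-adjusted models. Total second-stage length, named as an adjuster for the primary or secondary outcomes, includes time caused by failure and pulls the adjusted effect toward the null. The distortion is small if failure alone lengthens the stage (true RR 0.50 to about 0.51 to 0.55 for 10 to 30 added minutes). It is larger if training also shortens the stage (up to about 0.68 for a 10-minute reduction), and about nil if training changes neither failure nor length. All these sizes depend on inputs that the article does not give; the direction toward the null does not depend on the exact values chosen.

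General anaesthesia stands both as a secondary outcome and inside a covariate for secondary outcomes. Taken literally, that makes its own adjusted model uninformative, and it conditions other secondary outcomes on something that may follow a failed attempt. The unit-plus-period estimate is sound on this point.

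**What to change.** - State that the model with intervention, unit and time period gives the primary estimate, and label the covariate-adjusted models as supportive.
- Restrict those models to characteristics fixed before the first instrument is applied, for example maternal age, BMI, parity, previous caesarean or vaginal birth, gestation, birth weight and indication.
- Drop total second-stage length. Replace it with time to the decision or to first application only if that time is already recorded. It is not among the listed variables, and with data collection close to its end date, adding it could mean returning to the case notes.
- Use only analgesia in place before the attempt, and never adjust for general anaesthesia.
- Rotation and operator or supervisor grade may stay in a separately labelled sensitivity model, described as possible case-mix factors or mediators.

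If analgesia before the attempt cannot be separated from analgesia given later, leave it out. Apart from any new extraction, the change is to analysis wording. The cost is slightly less variance explained and less control for differences in second-stage length between periods.

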#### Sensitivity analyses

To account for any departure from the planned and scheduled intervention, i.e. for units which do not (fully) comply with or do not implement the intervention, a sensitivity analysis will test the effect of the intervention using the actual date of the intervention was first implemented. These analyses will be called “as implemented”. For units not compliant with the implementation schedule, births performed prior to the actual start of the intervention will be considered as “not exposed”, while births performed 3 months after the start of the first training session will be considered as performed during the “exposed” period. The same modelling strategy described in the previous section will be used.

We will also investigate the possibility to extend the analyses to the time-periods prior to this project to include a longer control period.

We do not anticipate that there will be extensive missing data for the primary outcome and our primary analysis strategy will be on complete cases. However, it is known that for a small number of births the attempt to perform an OVB is not collected. The main analyses will be conducted on complete-cases. We will then describe any missing data in detail, and if required, will test the robustness of our primary analysis using three approaches; all births with missing data will be considered as failed OVB, they will then be considered as successful OVB, and finally multiple imputations by chained equation will be conducted.

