## Abstract

**Background:**

Operative vaginal birth is a common procedure used to expedite birth after full cervical dilatation where there is a clinical need to do so (15% of births in the UK in 2016). The acquisition of skills for operative vaginal birth is dependent on the exposure of junior obstetricians to situations in which they can undertake directly supervised learning from senior accouchers. The Royal College of Obstetricians and Gynaecologists has recently introduced the first structured course in operative vaginal birth. To date, there have been no attempts to determine the clinical impact of a structured training package for operative vaginal birth.

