### Participants

The study population will consist of women and babies having an attempted OVB in the four maternity units during the study period (12 months per site, between 700 to 850 women per site, at least 3000 women in total).

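### The two fixed-value missing-data scenarios treat both phases alike, so they do not test missingness that differs before and after training, and they may count births not shown to be eligible

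*Protocol article*

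**What the plan says.** The Sensitivity analyses section of the protocol article does not expect extensive missing data on the primary outcome. It then gives a known exception: "it is known that for a small number of births the attempt to perform an OVB is not collected". The primary strategy is stated as "The main analyses will be conducted on complete-cases". Missing data are to be described in detail, and the authors, "if required, will test the robustness of our primary analysis using three approaches". In the first two, "all births with missing data will be considered as failed OVB, they will then be considered as successful OVB". For the third, "finally multiple imputations by chained equation will be conducted". No scenario separates pre-training from post-training births.

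Three other places matter:
- Participants defines who is studied: "The study population will consist of women and babies having an attempted OVB in the four maternity units during the study period". Inclusion criteria makes application of forceps or vacuum to the baby's head a condition of entry.
- Main analysis compares control periods with post-intervention periods.
- Main analysis uses modified Poisson regression, so the effect is a ratio of proportions.

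**The concern.** There are two separate difficulties.

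The first is what the scenarios can show. The quantity of interest is a contrast between phases. Missing data threaten it most when the unrecorded births differ from the recorded ones in one way before training and in another way after it. For example, training might change how carefully failed attempts are documented. Giving every missing birth the same value in both phases does not represent that pattern. A result that survives both scenarios could be reported as robust without having faced the relevant test.

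The second is which births are coded. The gap that the article names is whether an OVB was attempted, and an attempt is the entry condition. A birth with no recorded attempt has not been shown to belong to the study population. Coding it as a failed or a successful OVB may bring ineligible births into the denominator and, in the all-failed scenario, into the numerator. Imputing only its outcome would not settle eligibility either.

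**Working it through.** **Inputs.** Failure rates of 20% before and 10% after are the design values under Sample size (Conservative and Optimistic estimates). The article gives no missing share, so 1%, 2%, 5% and 10% of each phase are assumptions. The smaller effect, 20% v 15%, is also an assumption. The article states no figure for missing data, so there is none to reproduce.

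**Formula.** Let p0 and p1 be the observed failure rates before and after, m the missing share in each phase, and f0 and f1 the failure rates assigned to the missing births. Then

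RR = [(1 − m)p1 + m·f1] / [(1 − m)p0 + m·f0].

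**Planned scenarios.** With f0 = f1 = 0 (all successful), the factor (1 − m) cancels and RR = p1/p0 whatever m is. With f0 = f1 = 1 (all failed), m is added to both terms and RR moves towards 1.

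**20% v 10%, m = 5%.** Here 0.95 × 0.20 = 0.19 and 0.95 × 0.10 = 0.095.
- All successful: 0.095/0.19 = 0.50.
- All failed: 0.145/0.24 = 0.60.
- Success before, failure after: 0.145/0.19 = 0.76.
- Failure before, success after: 0.095/0.24 = 0.40.

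**Other missing shares, 20% v 10%**

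| m per phase | Planned pair | Opposite-direction pair |
|---|---|---|
| 1% | 0.50, 0.52 | 0.48, 0.55 |
| 2% | 0.50, 0.55 | 0.45, 0.60 |
| 5% | 0.50, 0.60 | 0.40, 0.76 |
| 10% | 0.50, 0.68 | 0.32, 1.06 |

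**20% v 15%, m = 5%.** Here 0.95 × 0.15 = 0.1425.
- Planned pair: 0.1425/0.19 = 0.75 and 0.1925/0.24 = 0.80.
- Adverse case (success before, failure after): 0.1925/0.19 = 1.01.

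Assuming 1500 observed births per phase and ignoring unit and period, the 95% intervals are 0.64 to 0.88 and 0.70 to 0.92 for the planned pair, and 0.88 to 1.17 for the adverse case.

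**Unequal missing shares, 20% v 10%.**
- 5% before and 2% after: the planned pair gives 0.098/0.19 = 0.52 and 0.118/0.24 = 0.49. The opposite-direction values are 0.118/0.19 = 0.62 and 0.098/0.24 = 0.41.
- 2% before and 5% after: the planned pair gives 0.095/0.196 = 0.48 and 0.145/0.216 = 0.67. The opposite-direction values are 0.145/0.196 = 0.74 and 0.095/0.216 = 0.44.

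**How extreme the adverse case is.** RR reaches 1 when f1 − f0 = (1 − m)(p0 − p1)/m. For 20% v 10% at m = 5% this is 0.95 × 0.10/0.05 = 1.9, which is impossible. For 20% v 15% at m = 5% it is 0.95 × 0.05/0.05 = 0.95, which needs almost complete discordance between phases.

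**Eligibility.** No arithmetic is needed. Participants and Inclusion criteria require an attempt with an instrument, while Sensitivity analyses names the attempt as the item that may be absent and then assigns an OVB outcome to all births with missing data.

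**The case against.** The scenarios are conditional, secondary checks. The primary analysis is on complete cases, little missing data is expected, multiple imputation is also planned, and the article claims a test of robustness, not bounds. Further scenarios could reasonably appear in a statistical analysis plan that is not shown. All of this stands, and it limits the weight of the point. It does not make the stated pair a test of phase-dependent missingness.

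Three stronger readings are tempting, and the article does not support them.

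- *The planned scenarios leave the effect unchanged.* That is true of the risk difference: at 5% missing, 0.095 − 0.19 and 0.145 − 0.24 are both −9.5 percentage points. The planned model gives a ratio, and on that scale the all-failed scenario moves 0.50 to 0.60. Only the all-successful scenario leaves the ratio fixed, and only when missing shares are equal.
- *Every birth with missing data has an unknown attempt.* The paragraph opens with missing primary-outcome data, so the phrase may also cover confirmed attempts with an unrecorded result. The eligibility point does not reach those births, although the between-phase point does.
- *The failure rate would be badly distorted.* Using the national figure in the Abstract ("15% of births in the UK in 2016"), 3000 OVBs imply 3000/0.15 = 20,000 births. If 1% lacked the field, 200 would be added, and coding all as failed would turn 20% into (600 + 200)/3200 = 25%. The 1% is an assumption, nothing says that all births enter the analysis file, and 200 extra on 3000 (6.7%) fits poorly with the article's expectation of "for a small number of births the attempt to perform an OVB is not collected". This figure should not be relied on.

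**Conclusion.** The point holds as a modest, inexpensive improvement to a secondary analysis. The planned pair does not bracket the between-phase contrast. At an assumed 5% missing per phase it spans 0.50 to 0.60, where opposite-direction coding spans 0.40 to 0.76. With a smaller observed effect (20% v 15%), both planned scenarios would still favour training while the adverse case shows no benefit.

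It would be wrong to infer that the primary result is at risk under the article's own expectations. At 1 to 2% missing and a true halving, the worst ratio is 0.60 and the conclusion stands. The gap matters only if missing data are more common or the effect is smaller. These ratios are crude, with no adjustment for unit or period, and the missing shares are assumed.

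The eligibility part needs no assumed number, but it applies only to births whose attempt is unrecorded.

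**What to change.** 1. Apply the fixed-value scenarios only to births with a confirmed instrument application and a missing first-instrument result.
2. Where the attempt itself is unrecorded, resolve it from the clinical notes that the study already reviews. If that fails, leave the birth out and report the number by unit and phase.
3. Add to the planned pair the two opposite-direction scenarios (missing counted as success before and failure after, and the reverse), or a tipping-point table over the two missing-failure rates f0 and f1.
4. Keep multiple imputation, restricted to the births in item 1.

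The cost is a few more model runs and some note checking for births with an unrecorded attempt. The reported sensitivity range will be wider than under the present plan. Complete-case analysis stays as the primary strategy.
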